##### Focus groups

Once the intervention completed, semi-structured focus groups will be conducted with participants and PE teachers, separately. The two peer coaches and two participants (randomly selected) from each intervention classes (*n* = 16) will be invited to the participants’ focus group, while all the PE teachers involved in the study will take part in the teachers’ focus group. Pre-determined open-ended questions will be asked during the focus group discussion, including feedback on enjoyment/usefulness of the *PRO-HIIT* intervention, continued use of the HIIT exercises and the perceived barriers and facilitators for doing/delivering the HIIT exercises. The template of the focus group questions is provided in the Additional File S2.

##### Confounding variables

An estimate of the age of peak height velocity will be used to assess the somatic maturation of participants (59). Participants’ PA and sleep at all time-points will be assessed by a Chinese version of the International Physical Activity Questionnaire, short form (IPAQ-SF) (60) and a validated Chinese version of the Pittsburgh Sleep Quality Index (PSQI) (61), respectively.

#### Statistical analyses

Data entry will be completed by one researcher with a random sample of at least 10% of entries cross-checked by a second researcher for accuracy. Prior to analysis, thorough checks for outliers and errors will be conducted using range and boxplot methods. Additionally, assessments for normality, homogeneity of variances and sphericity will be conducted as needed to verify assumptions. The baseline data for intervention and control groups will be presented and compared at individual level using independent sample *t*-test. An intention-to-treat approach will be adopted to evaluate the effects on outcome variables to avoid bias in exploring the impact of the intervention. Linear mixed-effect models will be used, with random effects, to analyse the impact of groups (intervention and control), timepoints (pre-, post-intervention and follow-up) and group × time interactions. Statistical analyses will be adjusted for the clustering effects at class level. Per protocol sensitivity analysis will be undertaken at the class level. Considering for disruptions such as school holidays, exams, severe weather, a minimum of 30 sessions is considered achievable over the 12-week period. Other sensitivity analyses, such as complete-case analysis, will be conducted where appropriate. Moderators, including sex (male, female), baseline overweight/obese (yes, no) and baseline CRF (healthy vs. needs to improve), will be examined with linear mixed models. Where appropriate, subgroup analyses will be conducted for the significant group-by-moderator interactions. PA, sleep and maturity will be included in the model to eliminate confounding effects. All data analyses will be conducted via IBM SPSS Statistics for Windows (SPSS 28.0; IBM Corporation, Armonk, NY, USA), with an alpha level of 0.05.

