### Sample size estimation

A sample size estimation was calculated based on CRF using the 20 m shuttle run test (20 m-SRT). Previous studies reported 9 laps of improvement, with effect size of *d* = 0.31 (36) and *d* = 0.69 (37), achieved through 12 or 14 weeks of resistance-based HIIT, respectively. In the current study, a conservative effect size of *d* = 0.31 was utilised for power calculation. Therefore, based on a G*Power (Version 3.1) calculation (38) and using two groups with 80% power at an α of 0.05, it is estimated to recruit 165 participants in each group. With an average enrolment of 50 students in secondary school classes in Ningbo and a conservative 20% of dropout rate (39), it is deemed that 8 classes (approximately 50 participants per class) would provide sufficient statistical power for analysis. Given the typical scale of a Chinese secondary school (10–15 classes per grade), the 8 classes will be recruited from one secondary school.

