### Outcome measurements

Outcome measurements will be conducted in the school premises by trained research assistants who will remain blinded to group allocation throughout all assessment time-points. All measurements will be introduced and explained during the training workshop and will be described again prior to the commencement of the measurements to ensure clarity. The measurements will be conducted during their regular PE lessons. Details of the outcome measures are summarised in Table 5.

**Table 5 T5:** How, when and where the outcome variables will be measured.

Outcomes	Tools	Timing	How and where (all participants, measured at class level)
Physical activity	GENEActiv	One week before and after intervention, first and last week of intervention.	A subsample of 60 participants (30 in each group, 30 males) will be randomly selected to wear the GENEActive accelerometer for 14 days consecutively for twice, covering the total 4 weeks.
Cardiorespiratory fitness	20 m shuttle run	T1, T2, T3	Multiple measurement stations will be held, and participants will be split into groups to ensure efficient measurements. Two physical education lessons are estimated to be sufficient. All these measurements will be conducted in sports hall.
Body composition	TANITA	T1, T2, T3	
Muscular strength	Handgrip, standing long jump	T1, T2, T3	
Bone health	GE Achilles	T1, T2, T3	
Executive function	Flanker tasks, visual 2-back tasks, colour-shape switch tasks	T1, T2, T3	Perform the executive function tasks online in a school computer room in one physical education lesson (40 min).
Wellbeing	SDQ	T1, T2, T3	Finish together using one physical education lesson (40 min) in a school computer room with the instruction of research staff.
Enjoyment	PACES	T1, T2, T3	
Motivation	BREQ-2	T1, T2, T3	
Affect	PANAS-SF	T1, T2, T3	
Self-efficacy	PPAS	T1, T2, T3	
Academic performance	End-of-term academic examinations	By the end of term 1 and T2	Obtained directly from head teacher.

SDQ, strength and difficulty questionnaire; PACES, physical activity enjoyment scale; BREQ-2, exercise regulations questionnaire; PANAS-SF, positive and negative affect schedule short form; PPAS, perceived physical ability scale; T1, pre-intervention; T2, immediately post-intervention; T3, 2-month follow-up.

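### No primary contrast is named: the listed group and group × time tests are not the end-of-training comparison behind the sample size, and the unspecified class adjustment may not protect group × time

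*Protocol article*

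**What the plan says.** Under Statistical analyses, the protocol article plans linear mixed-effects models with random effects "to analyse the impact of groups (intervention and control), timepoints (pre-, post-intervention and follow-up) and group × time interactions". It then states: "Statistical analyses will be adjusted for the clustering effects at class level". It does not say which random effects are fitted, which of the listed effects is the primary test, or how degrees of freedom are obtained. Sex, baseline weight status and baseline fitness are to be examined as moderators, and "subgroup analyses will be conducted for the significant group-by-moderator interactions".

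Under Sample size estimation, the target effect comes from earlier studies in which the gain in laps was "achieved through 12 or 14 weeks of resistance-based HIIT, respectively". The article continues: "In the current study, a conservative effect size of *d* = 0.31 was utilised for power calculation", and, "using two groups with 80% power at an α of 0.05, it is estimated to recruit 165 participants in each group".

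Four design facts bear on this:
- Classes are the randomised units, and there are eight (Study design).
- Randomisation takes place after baseline assessment and is stratified by PE teacher (Recruitment and allocation).
- Effectiveness and the change over the summer holiday are separate aims (Aims of the study).
- Testing is organised by class: "The measurements will be conducted during their regular PE lessons" (Outcome measurements). Table 5 also describes measurement at class level.

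**The concern.** There are two linked problems.

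First, the listed tests do not match the question the trial was sized for. The group effect averages over T1, when no intervention effect can exist. A two-way group-by-moderator term has the same fault. The three-visit interaction asks whether the arms differ in any pattern over time, including a difference that appears only after the holiday. A reader of the results could meet several candidate primary p-values, none of them the end-of-training difference in laps.

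Second, a class effect that is constant over time drops out of each class's change from T1 to T2. If that is the whole class adjustment, group × time is judged against pupil-level residual error although only eight classes were randomised. Anything that moves a whole class between visits (its test session, its teacher, its peer-coaches, its mood on the day) would then be counted as if it averaged out over about 160 pupils per arm, when it averages out over four classes.

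**Working it through.** **Inputs from the article.** d = 0.31; α = 0.05; power 80%; 165 per group; 8 classes of about 50; 20% dropout. That leaves 400 × 0.8 = 320 pupils, or 160 per arm and 40 per class. Four classes per arm is inferred from the focus groups: two coaches plus two pupils per intervention class gives 16, and 16 / 4 = 4.

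**Assumed, because the article gives no value.** Total variance is 1. Pupil correlation between visits, r, is 0.7–0.8. Class-by-time variance, s_ct, is 0, 0.01 or 0.02. Residual variance is s_e = 1 − r − s_ct.

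**1. The plan's own figure.** A two-sided two-sample t test at d = 0.31 with 80% power needs 165 per group (normal approximation 164; a one-sided test would need 130). The stated figure is reproduced. It belongs to an individually randomised comparison of two means at one time point.

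**2. Dilution of the group effect.** With zero effect at T1, d at T2 and f × d at T3, the average over visits is (0 + d + f·d)/3.
- f = 1: 0.62/3 = 0.21
- f = 0.5: 0.465/3 = 0.155
- f = 0: 0.31/3 = 0.10

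**3. What the interaction responds to.** In 20,000 simulated trials (8 classes of 40, three visits, intraclass correlation 0.05, no class-by-time variance, r = 0.8) there was no T2 effect and d = 0.31 at T3 only. The three-visit interaction rejected in 99.8% of runs; the T1–T2 contrast rejected in 5.1%.

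**4. Class-level protection if only class and pupil intercepts are fitted.** For the between-arm difference in T1–T2 change:
- Variance the model assumes: 4(s_e + s_ct)/160
- Actual variance: 4·s_e/160 + 4·s_ct/4
- Ratio R = (s_e + 40·s_ct)/(s_e + s_ct)
- Type I error, T1–T2 contrast (1 df): 2[1 − Φ(1.96/√R)]
- Type I error, three-visit interaction (2 df): exp(−5.991/(2R))

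| r | s_ct | R | T1–T2 contrast | 2-df interaction |
|---|---|---|---|---|
| 0.7 or 0.8 | 0 | 1.00 | 5% | 5% |
| 0.7 | 0.01 | 0.69/0.30 = 2.30 | 20% | 27% |
| 0.7 | 0.02 | 1.08/0.30 = 3.60 | 30% | 44% |
| 0.8 | 0.01 | 0.59/0.20 = 2.95 | 25% | 36% |
| 0.8 | 0.02 | 0.98/0.20 = 4.90 | 38% | 54% |

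A separate simulation agrees. Intraclass correlation 0.05 with class autocorrelation 0.8 means s_ct = 0.05 × 0.2 = 0.01. At r = 0.8 it gave 25% for the contrast and 37% for the interaction. With class-by-time variation as the error term, or with a class-level t test of T2 − T1 on 8 − 2 = 6 df, type I error stayed at about 5% in every setting.

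**5. Power of the interaction against the T2 contrast.** If the 1-df T1–T2 contrast has 80% power (noncentrality 7.85), the 2-df noncentrality is 7.85 × 2[1 + f² − (1 + f)²/3].
- f = 0.5: 7.85, power 71%
- f = 0.25 or 0.75: 8.50, power 75%
- f = 0 or 1: 10.47, power 83%

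So the interaction loses power only when the effect partly persists.

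**The case against.** The strongest reply is that the article describes a model in routine terms and leaves the random-effects structure and degrees of freedom to a fuller document. Unspecified random effects and an adjustment for class-level clustering are compatible with a class-by-time effect and Satterthwaite degrees of freedom. This stands. A reader might infer that the primary analysis has a false-positive rate far above 5%; the article does not support that. The inflation needs both an intercept-only model and classes that drift differently, and the article gives no variance from which to judge the second.

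The design also limits such drift. The primary-outcome section requires the same assistants, place, time of day and level of encouragement at every visit; assessors are blinded; randomisation is stratified by PE teacher. These measures reduce class-by-time variation. They do not remove differing class responses on the day or to different peer-coaches.

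A reader might also infer that the three-visit interaction always costs power. It does not: step 5 gives 83% if the effect wholly persists or wholly vanishes.

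Finally, a model with categorical time yields the T2 contrast directly, the aims separate effectiveness from the holiday change, and the sample size section does not itself name T2. All true. But the article lists the effects to be tested and that contrast is not among them. That the model could supply it does not make it the declared primary test.

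**Conclusion.** The mismatch between the listed tests and the powered comparison holds on the article's own text. T2 as the powered time point is an inference, though a strong one, from the source of the effect size and the separation of the aims. The averaged group effect keeps between one third and two thirds of a T2 effect when between none and all of it persists at T3. A group-by-moderator term without time is diluted in the same way. The interaction can be significant with no T2 effect.

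The class-level part holds conditionally: the wording does not secure protection for group × time. With a class intercept alone and the assumed 1–2% class-by-time variance, type I error would be about 20–38% for the T1–T2 contrast and about 27–54% for the 2-df interaction. With zero variance it would be about 5%. These are sensitivity figures, not estimates for this trial.

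**What to change.** State one primary test: the between-arm difference in 20 m shuttle run laps at T2, adjusted for T1 laps, either as a covariate or by constraining the arm means to be equal at T1. Include a class-by-time random effect, or a class random effect in a model of the T2 outcome, or analyse class-level summaries. Use Satterthwaite or Kenward–Roger degrees of freedom: about 6, fewer if PE-teacher strata are fitted. Make T3 a secondary contrast. Test moderators on the T2 contrast (group × time × moderator in the three-visit model), not on a two-way term averaged over visits.

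This changes only analysis wording and uses data already planned. The cost is wider confidence intervals. With class-level error, power of the simple T2 − T1 contrast for d = 0.31 (assumed r = 0.8, intraclass correlation 0.05) was 96%, 75%, 57% and 33% at class autocorrelations of 1.0, 0.9, 0.8 and 0.5. That loss reflects having eight randomised classes, and is better seen in the interval than hidden by the model.

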### Intervention delivery and exercise design

The present study is a quality PE/PA intervention in which a resistance-based HIIT session is embedded in the first 6–10 min of regular PE and PA lessons, replacing traditional warm-up activities. The intervention will be delivered five times a week—three PE and two PA lessons—over twelve weeks (from school term 2, week 5 to week 16, March to June 2024). Throughout the intervention, PE teachers will coordinate and supervise the HIIT intervention, while the delivery will be accomplished by two student peer-coaches, selected by the PE teacher within each intervention class. The control group will maintain their traditional warm-up activities, such as light running and static stretching.

To ensure quality and effective implementation, the leading researcher will collaborate with the PE teachers and peer-coaches for delivering the intervention during the initial two weeks. Researchers will visit the school once per month to provide on-going support and guidance. Additionally, a training logbook at each intervention class will be maintained by the PE teachers to document aspects, such as attendance, dose delivered and received, and adverse events. These records will be sent to researchers on a weekly basis to ensure prompt feedback and communication. In cases where HIIT sessions are cancelled due to inevitable factors such as large school events or severe weather, participants will be encouraged to complete these sessions during alternative times (e.g., breaks). These additional sessions will be supervised by peer-coaches and will be recorded in the training logbook. The control group will take their regular PE and PA lessons as usual.

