#### Process evaluation

A comprehensive process evaluation will be conducted for the *PRO-HIIT* intervention, which will be guided by the MRC process evaluation framework (27). The framework contains three domains, including implementation (i.e., fidelity, reach, recruitment and retention, dose delivered and adaptation), mechanisms of impact (i.e., mediators, dose received, unintended consequences and response) and context (i.e., barriers, facilitators, and contamination). The MRC framework, in conjunction with insights from a recent school-based HIIT review by Liu et al. (23), will guide the adaptation of process evaluation measures tailored specifically to *PRO-HIIT*, as detailed in Table 3.

**Table 3 T3:** Medical research council definition for process evaluation and its application to the *PRO-HIIT* intervention.

Measurements	MRC definition	Apply to *PRO-HIIT*	How
Implementation: The process through which interventions are delivered, and what is delivered in practice.			
Fidelity	The consistency of what is implemented with the planned intervention.	HIIT intensity.	HR and RPE
Reach	The extent to which a target audience comes into contact with the intervention.	Schools or participants contacted.	Recruitment
Dose delivered	How much intervention is delivered.	HIIT session length, frequency and intervention duration/sessions in the protocol.	Protocol
Recruitment & retention	NG	Number of participants who are randomised and completed the intervention.	Training logbook and outcome assessment
Adaptation	Alterations made to an intervention in order to achieve better contextual fit.	Changes being made to facilitate *PRO-HIIT*.	Training logbook and teachers’ focus group
Mechanisms of impact: The intermediate mechanisms through which intervention activities produce intended (or unintended) effects.			
Mediator	Intermediate processes which explain subsequent changes in outcomes.	Mediators (e.g., sex, baseline CRF and BMI) influencing the outcome assessment.	Data analysis
Dose received	NG	HIIT sessions participants performed.	Training logbook
Unintended consequences	NG	Adverse events or other unanticipated fairs recorded.	Training logbook
Response	How participants interact with a complex intervention.	Feedbacks from participants and teachers.	Focus group and questionnaire
Context: Factors external to the intervention which may influence its implementation, or whether its mechanisms of impact act as intended.			

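### Table 3 takes dose delivered from the protocol instead of the training logbook, so that row returns the 60 planned sessions whatever was actually run

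*Protocol article*

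**What the plan says.** **Planned dose.** Under Intervention delivery and exercise design: "The intervention will be delivered five times a week—three PE and two PA lessons—over twelve weeks".

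**Dose delivered.** In Table 3 (Process evaluation) this item sits in the implementation domain, which concerns what happens in practice. The MRC definition given for it is "How much intervention is delivered". The trial's own version is "HIIT session length, frequency and intervention duration/sessions in the protocol", and the column that names the source gives the protocol.

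**Dose received.** Table 3 has a separate row for this, "HIIT sessions participants performed", taken from the training logbook.

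**Logbook.** The intervention section has PE teachers keep one in each intervention class "to document aspects, such as attendance, dose delivered and received, and adverse events", and send the records to the researchers weekly. It foresees cancelled sessions being made up at other times: "These additional sessions will be supervised by peer-coaches and will be recorded in the training logbook".

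**Per protocol.** Under Statistical analyses, intention to treat is the main approach. Then: "Per protocol sensitivity analysis will be undertaken at the class level". The next sentence, after naming likely disruptions, adds that "a minimum of 30 sessions is considered achievable over the 12-week period".

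**The concern.** A delivery measure read from the plan cannot depart from the plan. The row would show full delivery in a class that lost many sessions and in a class that lost none.

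This matters because the process evaluation is the trial's third aim, and the Discussion presents it as a novelty of the study. The Discussion also says that most school programmes of this kind ran two to three times a week, and that five times a week is the less studied frequency. If the reported frequency is the planned one, a reader cannot tell from this row whether five a week was achieved.

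The per-protocol wording raises a related, smaller question. An analysis set at class level speaks to what the class delivered. Pupils in one class can differ widely in what they attended, so the result could be misread as the effect of doing the sessions.

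**Working it through.** **1. Planned total.** The article does not print a total. It follows from the stated schedule: 5 sessions per week × 12 weeks = 60 sessions.

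**2. What the Table 3 row returns.** Its inputs are the planned length, frequency and number of sessions, so its value is 60 for every class. Suppose a class runs D sessions. True delivery is D/60 and the row shows 60/60. At D = 30, true delivery is 30/60 = 50%, or 30/12 = 2.5 sessions a week, against five a week in the row. The article expects some D below 60: it allows for cancellations through school events and weather, and the statistical section adds holidays and exams.

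**3. Passages side by side.**

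| Place | Dose delivered is | Source |
|---|---|---|
| Table 3, definition | the amount delivered | – |
| Table 3, application | the planned amount | protocol |
| Intervention section | an item that teachers record | training logbook |

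The first and third rows agree. The second does not fit either.

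**4. Class delivery and pupil receipt.** This step bears on the per-protocol wording. There are 4 intervention classes, because the focus groups take 4 pupils per intervention class and 16 in all. A class-level rule keeps or removes about 50 pupils at a time. To see how far class delivery stands in for pupil receipt, assume that each pupil attends each session independently with probability a. Then the share of pupils with at least 30 sessions is

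P(X ≥ 30), with X ~ Binomial(D, a).

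Both D and a are assumptions, since the article gives neither.

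| Class delivers D | Attendance a | Share of pupils with 30 or more |
|---|---|---|
| 30 | 80% | 0.1% |
| 30 | 90% | 4% |
| 30 | 95% | 22% |
| 36 | 70% | 5% |
| 36 | 80% | 40% |
| 36 | 90% | 94% |
| 45 | 70% | 75% |
| 45 | 80% | 99% |
| 60 | 50% | 55% |
| 60 | 70% | about 100% |

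Class delivery is a poor guide to pupil receipt when delivery is near 30, and mostly an adequate one when delivery is well above it.

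**The case against.** The strongest reply is that the information is collected and will be reported. The dose-received row uses the logbook, make-up sessions are logged, and adaptations are logged and also raised in the teachers' focus group. On that view the dose-delivered cell is simply the planned amount, set beside the amount received. Part of this stands: the process evaluation as a whole would not report full delivery, and the flaw is confined to one row. But that row is labelled and defined as delivery, and planned dose set against received dose cannot separate sessions that were never run from sessions that pupils missed.

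A reader might infer more from the per-protocol sentence: that a class enters if and only if it ran 30 sessions, so the analysis either repeats intention to treat or deletes a whole randomised class (leaving 7 classes, 7 − 2 = 5 degrees of freedom). The article does not support this. It gives the level of the analysis but never says that 30 is the inclusion criterion, and the detailed definition may stand in the full protocol or analysis plan. A class-level check is also legitimate for an intervention delivered to whole classes and interrupted by events that affect whole classes. Agreement with intention to treat would be informative. Any per-protocol set departs from randomisation, including one built on pupils' attendance.

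Nor should dose delivered be faulted for not showing the effect of receiving the intervention. It is a descriptive process measure and is not offered as an effect estimate.

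**Conclusion.** The Table 3 inconsistency holds. As written, dose delivered equals the 60 planned sessions by construction, contrary to the table's own definition and to the stated purpose of the logbook. The size of the misstatement in any class is the shortfall from 60, which is unknown in advance. It would be half the planned dose in a class that ran 30 sessions, and nothing in a class that ran or made up all 60.

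The per-protocol point is secondary and concerns interpretation. The 30 sessions are half of the plan, but the article leaves open whether they are the criterion and what they count. Whatever the criterion, a class-level analysis estimates the effect in classes that delivered the programme. The attendance figures above are illustrative and only show why the distinction can matter.

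The intention-to-treat result, the sample size and the power calculation are unaffected.

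**What to change.** 1. In Table 3, change the source of dose delivered to the training logbook. Report, for each intervention class, the sessions and minutes actually run, including logged make-up sessions, against the 60 sessions planned and their planned length. The planned figures can stay beside them, labelled as planned.
2. Under Statistical analyses, state whether 30 sessions is the per-protocol criterion and whether it counts sessions delivered by the class or attended by the pupil. Describe the class-level result as the effect in classes that delivered the programme.
3. Optional: add a pupil-level analysis using logged attendance, as supportive only. It has real limits. A complier-average analysis cut at 30 sessions assumes that pupils below 30 gain nothing, and clustered standard errors from 8 classes are unreliable.

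Items 1 and 2 cost only wording, because teachers already record delivery and attendance. No new data collection is needed.

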#### Primary outcome

##### Cardiorespiratory fitness

CRF will be assessed using the 20 m-SRT, a well-established field test for evaluating CRF (43). The 20 m-SRT requires participants to run back and forth between two lines positioned 20 meters apart. Participants must reach the other end before a designated beep sounds. The beep is set to allow the participants to start at 8.5 km/h with increases in speed of 0.5 km/h denoted by a triple beep. The test concludes if a participant fails to complete two consecutive shuttles or volitionally discontinues. Performance on the 20 m-SRT will be reported as number of laps completed. The test will be administered by the same group of research assistants at the same location, time of the day and with consistent levels of verbal encouragement across all measurement timepoints to avoid biased results.

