##### Body composition

Height and waist circumference will be measured with a portable stadiometer and a tape, respectively. Subsequently, waist-to-height ratio will be calculated (45). Body mass and body fat percentage will be determined with a Tanita device (Tanita Corp., Tokyo, Japan).

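### Baseline fitness and weight status are tested as two-category moderators although both can be used as numeric scores, which weakens the interaction tests if moderation is roughly linear

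*Protocol article*

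**What the plan says.** The Statistical analyses section names three moderators to be examined with linear mixed models. Sex is naturally binary. The other two are given with their categories: "baseline overweight/obese (yes, no") and "baseline CRF (healthy vs. needs to improve"). The follow-on step is that "subgroup analyses will be conducted for the significant group-by-moderator interactions".

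Both underlying quantities are measured on numeric scales:

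- Under Cardiorespiratory fitness: "Performance on the 20 m-SRT will be reported as number of laps completed".
- Under Body composition: "Height and waist circumference will be measured with a portable stadiometer and a tape", and "Body mass and body fat percentage will be determined with a Tanita device". BMI follows from height and mass.

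Table 3 (Process evaluation) lists the same variables without categories: "Mediators (e.g., sex, baseline CRF and BMI) influencing the outcome assessment". Its label, mediators, disagrees with the Statistical analyses section, which calls them moderators. That is a separate matter.

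The article describes no continuous version of the moderator test. It gives no cut-points, no expected share of pupils in each category and no power for moderation.

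**The concern.** A two-way cut treats pupils just either side of the boundary as different, and all pupils on one side as alike. When the effect of the intervention changes gradually with baseline fitness or weight, most of that gradient lies within the categories, where the test cannot see it. The interaction estimate becomes less precise and depends on where the cut is placed.

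This matters more because the trial is sized for the main effect only. The Sample size estimation section works from one between-group difference ("a conservative effect size of *d* = 0.31 was utilised for power calculation") and makes no allowance for moderation. The interaction test is also a gate: subgroup analyses follow only if it is significant. A weakened test therefore decides whether differential benefit is looked at further.

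**Working it through.** **The plan's own figure.** Inputs from Sample size estimation: d = 0.31, 80% power, α = 0.05 (two-sided assumed).

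- Normal approximation: n per group = 2 × (1.960 + 0.842)² / 0.31² = 163.4, so 164.
- Exact t calculation: 165, with power 80.2%. The stated 165 per group is reproduced. A one-sided test would give 129, so the figure is two-sided.

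This figure concerns the main comparison and says nothing about moderation.

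**Pupils available.** 8 classes × about 50 = about 400. After the planned 20% dropout, 400 × 0.8 = about 320.

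**Information kept after a cut.** For a linear interaction, the efficiency of a binary moderator relative to the continuous one is the squared correlation between the score and its indicator. For a normal score with share p in the smaller category:

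efficiency = φ(z_p)² / [p(1 − p)]

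- p = 0.5: 0.3989² / 0.25 = 0.637
- p = 0.3: 0.3477² / 0.21 = 0.576
- p = 0.2: 0.2800² / 0.16 = 0.490
- p = 0.1: 0.1755² / 0.09 = 0.342

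The effective number is 320 × efficiency. Power, for an interaction that would have 80% power with the continuous score, is Φ[(1.960 + 0.842) × √efficiency − 1.960].

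| Split | Information kept | Lost | Effective N of 320 | Power by formula | Power simulated |
|---|---|---|---|---|---|
| 50/50 | 64% | 36% | 204 | 61% | 56% |
| 30/70 | 58% | 42% | 184 | 57% | 52% |
| 20/80 | 49% | 51% | 157 | 50% | 45% |
| 10/90 | 34% | 66% | 110 | 37% | 30% |

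The simulation used N = 320 individuals without clustering and 4,000 runs per split. The continuous test had 78% to 80% power in the same runs. Simulated power after the cut is lower than the formula because the score also predicted the outcome (slope 0.5), and the cut leaves part of that variation in the residual.

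**Sensitivity to shape.** The documents give no distribution for either score. For a right-skewed score (gamma, shape 4), the loss depends on which tail is cut:

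- lowest 30% cut off: 55% lost; lowest 20%: 66% lost
- highest 30% cut off: 36% lost; highest 20%: 40% lost

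**Assumptions, none of them from the documents:** the split, the distribution, a linear change of effect with the moderator, and a category that is a simple cut on the same numeric score.

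**The case against.** The strongest defence is that these are health categories and not arbitrary median splits. Whether pupils in the at-risk group respond differently is a fair practical question for a school programme. Moderation is also not named in the Aims of the study. This supports keeping the categories for reporting and explains why the point is minor. It does not justify using them for the test, because a continuous model can still report the estimated effect for each category.

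A second objection concerns the remedy, and it stands. The planned model takes pre, post and follow-up values as the outcome. If raw baseline laps were added as a moderator of the fitness outcome, they would be both the T1 response and the moderator. At T1 the two are identical, so residual variance would differ sharply by time point and the time-by-moderator term would pick up regression to the mean. A slope on raw laps could also partly reflect sex or maturity. The fix below allows for both.

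Three stronger readings are tempting but not supported:

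- *That the cut certainly discards a third to a half of the information.* For a normal score and linear moderation, that range needs about 21% to 50% of pupils in the smaller category. The documents do not give the split. With fewer pupils, or a skewed score cut in its lower tail, the loss is larger. With a true threshold at the cut there is none.
- *That the plan rules out a continuous test.* The list of moderators is introduced as non-exhaustive, and Table 3 names baseline CRF and BMI without categories. A continuous version is not described, but it is not excluded.
- *That eight classes make these interaction tests weak.* Fitness and weight status vary among pupils within a class, so with a class random intercept the interaction draws mainly on within-class variation. The number of classes would be the main limit only if moderator slopes differed between classes, and the documents give no basis for that.

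**Conclusion.** The point holds in conditional form. The article fixes two moderators as binary although the trial measures the underlying quantities numerically. If moderation is roughly linear and the score roughly normal, the interaction test loses at least about 36% of its information, rising to about 51% at 20/80 and 66% at 10/90. An interaction detectable with 80% power on the continuous score would then have about 61% power at best by formula, or 56% in simulation.

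The 36% floor belongs to the normal shape and to linear moderation; neither can be checked from the article. The moderator tests are secondary and the primary comparison of fitness between groups is untouched. This is a worthwhile improvement, not a flaw in the trial's main conclusion.

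**What to change.** - Test the group-by-moderator interaction with baseline laps and baseline BMI (or BMI z-score) as continuous moderators, and add a quadratic term to check linearity.
- For the fitness outcome, use T2 and T3 laps as the response, with baseline laps as covariate and moderator, so that baseline is not on both sides of the model. Include sex and maturity, and keep the adjustment for class.
- Keep the two fitness categories and the overweight/obese categories to present estimated effects, and state their cut-points in advance.

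No new data are needed and the models remain linear mixed models. The cost is a linearity assumption, which the quadratic term checks, and a small change in the structure of the moderator model for the fitness outcome.
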